#### Intervention

In addition to the usual hospital care, patients randomized to the intervention group will be provided with a supervised outpatient exercise training program, according to the results of the exercise stress test performed one month after hospital discharge and bearing in mind the physical limitations imposed by co-morbid conditions. The program will be performed in the hospital and it will start within the three days after the exercise stress test. It will comprise three hours a week (spread over three alternate days) of supervised exercise training for 10 weeks. The intervention will end after 10 weeks, regardless of whether the patients have completed 30 sessions. Exercise classes will be supervised by a physiotherapist and will consist of 10 minutes of warm-up and muscle stretching, 30 minutes of aerobic exercises (cycloergometer), 15 minutes of isotonic exercises for the upper and lower extremities and 5 minutes of cool-down. Moreover, instructions will be given on self-pulse counting, subjective perception of effort using the Borg scale, relaxation exercises, breathing techniques, postural health and minimizing physical effort. Aerobic exercise intensity will be between 75-90% of the maximum heart rate obtained in the previous exercise stress test and progressing according to the rating of perceived exertion (RPE: Borg scale 11–15). Resistance training will be performed with 10–15 repetitions for three sets, maintaining an RPE of 11–14. The physiotherapist will check that patients are exercising at their prescribed intensity with a pulse oximeter (Quirumed® Health & Care).

After hospital discharge, patients in both groups will have scheduled follow-up visits with a cardiac nurse at the first month, and then after 3, 6 and 12 months (visits 1, 2, 3 and 4 respectively) since hospital discharge in order to control the risk factors, reinforce education for disease control and review adherence to cardiac medication and CRP follow-up.

Control patients will be asked to complete the same outcome measures as the intervention group (See Figure 1).

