### Data collection and measures

#### Procedure

Each day, the cardiac nurse and the physiotherapist will check the bed list of patients admitted to the Cardiology Department. They will select the eligible patients after assessing the clinical history and consulting the cardiologist. In the inpatient setting, the cardiac nurse or the physiotherapist will give verbal and written information related to the study to eligible patients and will resolve all the patients’ doubts. These professionals will stress to the patient that the randomization process will decide the group inclusion. Before discharge (visit −1), eligible patients who agree to participate will be asked to give signed informed consent. In this visit, the cardiac nurse will record the following variables: education level, marital status, living situation, employment status and comorbidities (Charlson Comorbidity Index). On discharge (visit 0) the cardiac nurse or the physiotherapist will contact the Clinical Research Unit regarding the randomization process. Once the cardiac nurse or the physiotherapist knows the randomization group, they schedule the patient for the first cardiac nurse visit and for the exercise stress test.

Patients will attend four cardiac nurse visits (visits 1, 2, 3 and 4). During these visits, the cardiac nurse will describe ways of improving cardiovascular risk factors and cardiac medication adherence, and will answer the patients’ questions. The following variables will be recorded: attendance, systolic blood pressure (SBP), diastolic blood pressure (DBP), heart rate, Body Mass Index (BMI), abdominal circumference, Mediterranean diet, depressive symptoms (Yesavage Geriatric Depression Scale), basic activities of daily living (Barthel index), tobacco dependence (Fargeström test), compliance with cardiac medication (Haynes-Sackett test), taking sublingual nitroglycerin, hospital emergency visits, hospital readmissions and mortality. Quality of life (EuroQol5) will be recorded at all visits except visit 3. To address a possible cross-over effect, all patients will be asked to complete a physical activity questionnaire (Capersen and Powell classification) at baseline and in each follow-up visit. This test categorizes physical activity in four levels: sedentary, irregular activity, non-intensive regular activity, and intensive regular activity.

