Additional information will be recorded in the intervention group. Between visits 1 and 2, intervention patients will attend the training sessions. All sessions will be supervised by the physiotherapist. In each session the following values will be compiled: heart rate (initial, maximum, final), oxygen saturation (initial, during session, final), SBP (start, during session, final), DBP (initial, during session, final), degree of dyspnea (initial, final) and the level on the Borg scale. For each patient, the physiotherapist will compile the data from the exercise sessions and the number of physical sessions attended.

The cardiac nurse or physiotherapist will record the cause of withdrawal during the follow-up. The cardiac nurse will collect all data and enter them in a database designed for this study.

Table 1 summarizes the measures and variables according to the timeline.

**Table 1 T1:** Summary of measures and variables according to the timeline

**VISIT**	**−1**	**0**	**1**	**2**	**3**	**4**
**Time (months)**	**−1**	**0**	**1**	**3**	**6**	**12**
**Inclusion/exclusion criteria and informed consent**	X					
**Sociodemographic data** (sex, age, education level, marital status, living situation, employment status) and **comorbidity** (Charlson Index))	X					
**Cardiovascular risk factors** (diet, alcohol, tobacco dependence - Fargeström test - hypertension, diabetes, exercise practice, family heart disease), **dyspnea**, **depressive symptoms** (Yesavage Depression Scale) and **activities of daily living** (Bartel Index)	X		X	X	X	X
**Random allocation**		X				
**Diagnostic reason for referral** (localization, severity, number of stents, ejection fraction)			X			
**Medication prescribed**			X			
**Exercise stress test** (theoretical maximum heart rate, real maximum heart rate, baseline heart rate, chronotropic index, level reached, recovery time of the initial heart rate - 1 and 3 minutes-)			X	X		
**Level of risk for cardiac rehabilitation**			X			
**Control blood test**			X	X		X
**Anthropometric measures** (Body Mass Index, abdominal circumference)			X	X	X	X
**Systolic and diastolic blood pressure** and **baseline heart rate**			X	X	X	X
**Physical activity** (Capersen and Powell classification)			X	X	X	X
**Quality of life** (EuroQol5)			X	X		X
**Cardiac medication adherence** (Haynes-Sackett method) and **taking sublingual nitroglycerin**			X	X	X	X
**Adherence to Cardiac Rehabilitation Program**			X	X	X	X

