### Statistical issues

#### Sample size

To ensure a statistical power of 80% in order to detect differences in the contrast of the null hypothesis (H_0_: equal percentages of cardiac readmissions in the two groups) through a two-tailed chi-square test for two independent samples, with a level of significance of 0.05, and assuming that the percentage of cardiac readmissions in the control group is 25% and the percentage in the intervention group is 12%, each group will require 139 patients. Assuming a 5% loss to follow-up, we estimate that 146 patients will be needed in each arm.

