#### Statistical analysis

Continuous variables will be summarized using means and standard deviations for normal distributions, and by medians and the 25th and 75th percentiles for non-normal distributions. Categorical variables will be summarized using absolute values and relative frequency. We will test for significant differences among the baseline characteristics of the control and intervention groups. For continuous variables, we will use the Student's *t*-test if both sample groups have normal distribution or the Mann–Whitney *U* test otherwise. We will use the *χ*^2^ test to compare categorical variables (or Fisher’s exact test in 2×2 contingency tables where the expected frequencies are lower than 5).

Percentage of patients readmitted for cardiac disease will be analysed through a two-tailed *χ*^2^ test for two independent samples, and time to first hospital readmission for cardiac disease will be analysed as time to event with Kaplan-Meier estimation and Cox proportional regression models. The deaths occurring without hospitalization will be introduced in the survival analysis as censored data. Event or censored times for all patients will be measured from the time of randomization (visit 0). All information available on the primary and secondary end points will be collected until the time of final contact with the patient, including patients lost to follow-up, at which point follow-up will be censored. Survival data will be presented graphically using the Kaplan-Meier method. We will use the log-rank test to compare the survival curves. To estimate the effect size, we will report the unadjusted hazard ratios (HR) and associated 95% confidence intervals (95% CI) obtained in the bivariate Cox proportional regression models.

To establish whether the allocation group is an independent prognostic factor for cardiac readmission, we will adjust for potential confounders in a multivariate analysis. The model will be adjusted with the significant covariates in bivariate analysis or those that were clinically significant. To estimate the effect size, we will report the adjusted hazard ratios (HR) and associated 95% confidence intervals (95% CI) obtained in the multivariate Cox proportional regression models.

Outcomes will be analysed on an intention-to-treat basis. A two-sided α-level of 0.05 will be considered statistically significant. Data will be analysed using IBM SPSS Statistics for Windows v.20 and Stata v.10.

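### Allocation is opened about a month before training starts: the primary window begins with no planned contrast, and Table 1 gives EuroQol and activity no pre-allocation value

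*Protocol article*

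**What the plan says.** All references are to the protocol article.

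- **Allocation.** Under Procedure and in Table 1, randomisation takes place on discharge (visit 0). The nurse or physiotherapist then learns the arm and books visit 1 and the stress test. Limitations confirms that patients and staff know the assignment.
- **Start of training.** Under Intervention, training is planned "according to the results of the exercise stress test performed one month after hospital discharge" and starts within three days of it.
- **Event clock.** Under Statistical analysis: "Event or censored times for all patients will be measured from the time of randomization (visit 0"). The primary outcomes cover the first year after discharge, and analysis is by intention to treat.
- **Planned effect.** Under Sample size, cardiac readmission is assumed to be 25% in controls and 12% with training. The comparison is made "through a two-tailed chi-square test for two independent samples, with a level of significance of 0.05", with 80% power and 139 patients per arm. The section does not mention the month before training.
- **First measurements.** Table 1 first marks the stress test, EuroQol and the activity classification at visit 1 (month 1). The Procedure text on EuroQol, read with the four nurse visits it follows, agrees with this. On activity the Procedure text says something else: "all patients will be asked to complete a physical activity questionnaire (Capersen and Powell classification) at baseline and in each follow-up visit".
- **What is taken before allocation.** Table 1 marks exercise practice, diet, tobacco, dyspnoea, depressive symptoms, activities of daily living, sociodemographic data and comorbidity at visit -1.

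**The concern.** Both arms are planned to receive the same care from discharge until training begins. Readmissions in that period count fully in the primary outcome but cannot be prevented by training, so they pull the one-year comparison towards no difference. The Cox model reports one hazard ratio over a period expected to have a ratio near 1 at first and a different ratio later. A reader needs to know whether the 12% planning figure already absorbs this.

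The second issue is the timing of first measurement. Functional capacity and quality of life are secondary outcomes, and the activity questionnaire is the stated check for cross-over. If all three are first recorded after patients have known their arm for a month, the first value may already reflect that knowledge. A control patient who takes up exercise on learning the allocation would look active from the start, and the cross-over would go undetected.

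**Working it through.** **Step 1: reproduce the plan's figure.** Inputs from Sample size: p₁ = 0.25, p₂ = 0.12, two-sided α = 0.05, power 80%. With p̄ = 0.185, pooled variance and no continuity correction:

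n = [1.960·√(2·0.185·0.815) + 0.842·√(0.25·0.75 + 0.12·0.88)]² / 0.13² = (1.076 + 0.456)² / 0.0169 ≈ 138.9, so **139 per arm**.

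The stated figure is reproduced. Power at 139 is 80.0% by this formula and 80.7% by exact enumeration.

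**Step 2: reading A, the planned ratio acts only once training has started.** The planning ratio is 0.12/0.25 = 0.48. Let *f* be the share of first-year control readmissions that fall before training. The documents do not give *f*. It is assumed to run from 1/12 (constant risk) to 30% (front-loaded). Then

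p₂ = 0.25·f + 0.25·(1 − f)·0.48.

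For f = 1/12: 0.0208 + 0.2292·0.48 = 0.1308. Power at n = 139 per arm is Φ{[(p₁ − p₂)√n − 1.960·√(2p̄(1 − p̄))] / √(p₁(1 − p₁) + p₂(1 − p₂))}. For f = 1/12 this is Φ{(1.405 − 1.088)/0.549} = Φ(0.577) = 0.718.

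**Step 3: reading B, 12% is the whole-year rate.** Then 139 and 80% stand. The ratio needed after training starts is (0.12 − 0.25f)/(0.25 − 0.25f). For f = 1/12 this is 0.0992/0.2292 = 0.43.

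| Assumed early share f | A: intervention rate | A: power at 139 per arm | A: n per arm for 80% | B: ratio needed after training starts |
|---|---|---|---|---|
| 1/12 | 13.1% | 72% | 170 | 0.43 |
| 20% | 14.6% | 59% | 230 | 0.35 |
| 25% | 15.3% | 53% | 265 | 0.31 |
| 30% | 15.9% | 47% | 308 | 0.26 |

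Exact power at the first three shares is 72.3%, 58.8% and 52.8%.

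**Step 4: the hazard ratio.** The planned percentages imply a hazard ratio of ln(0.88)/ln(0.75) = 0.444. If that applies only after training starts, with ratio 1 before, the average weighted by cumulative hazard is f + (1 − f)·0.444. This gives 0.49 at f = 1/12 and 0.56 at f = 20%. Converting these back to one-year percentages gives power of 71% and 57%, close to reading A.

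**Step 5: how much a first-month estimate can show.** Expected control readmissions are 139 × 0.25 = 34.75. At f = 1/12 about 3 fall before training, and at f = 25% about 9. A hazard ratio for that period would be very imprecise.

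**Step 6: measurement schedule.** On activity, Procedure promises a baseline value in addition to each follow-up visit, while Table 1 marks "Capersen and Powell classification" at visits 1 to 4 only. The two cannot both describe the schedule, unless visit 1 is meant as baseline, which the text lists as a follow-up visit. For EuroQol the text and Table 1 agree, and both place the first value after allocation.

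**The case against.** **The quoted sentence is right.** Randomisation is the proper origin for an intention-to-treat analysis. A reader might infer that the clock should start at visit 1 or at the first session. With allocation left at discharge, that would drop events after randomisation and risk selection. This objection stands in full.

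**The power loss depends on a reading.** A reader might infer that the trial is undersized. Sample size gives 25% and 12% as group percentages and does not limit the effect to the trained period. Read as whole-year rates, they give exactly 139 per arm. The early share is also assumed. This stands: the documents show an unstated assumption, not a sample size error.

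**Non-proportional hazards do not invalidate the analysis.** The sample size rests on a chi-square test of percentages, which needs no such assumption. The log-rank test keeps its validity under the null, and an overall hazard ratio can be read as an average. A ratio of exactly 1 in month 1 is also only an expectation in an open trial. What remains is a point about interpretation.

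**Baseline data are not absent.** Many covariates, including exercise practice, are taken at visit -1, and visit 1 precedes training. The claim holds only for EuroQol, the activity classification and the stress test, and only in that their first value follows open allocation. No size of bias can be shown from the documents.

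**Randomising at visit 1 is a trade-off.** It would give all three measures a pre-allocation value. With 139 per arm randomised then, and patients readmitted in month 1 not randomised, exact power is 77% under constant risk (23.4% v 11.2%) against 72% under reading A. But early events would leave the outcome and early losses would leave the population. The window would no longer be the first year after discharge, and Limitations already expects difficulty in including patients. The documents do not support calling this a required correction.

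**Conclusion.** The concern holds in a limited form. Allocation is open from discharge and training follows about a month later, so roughly one-twelfth of the primary window has no planned contrast. Neither Sample size nor Limitations says so. The consequence depends on what 12% means. If 0.48 is the effect of training once begun, power is about 72% under constant risk and 47% if 30% of readmissions come early. If 12% is a whole-year rate, the planned power stands, but training must achieve a ratio of about 0.43 or stronger after month 1. Both rest on no effect before training and on an assumed early share.

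Separately, EuroQol, the activity classification and the stress test have no value in Table 1 from before allocation was known, and for activity the text and the table disagree. This calls for a modest improvement. It does not show an invalid primary analysis or a need to redesign the trial.

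**What to change.** Keep randomisation and the event clock at visit 0, and:

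1. Add EuroQol and the Caspersen-Powell classification to visit -1 in Table 1, keep the visit 1 values, and align the Procedure text with the table. Adjust the quality-of-life and activity comparisons for the visit -1 values. The stress test stays at visit 1, so its first value should be described as before training but after allocation.
2. Pre-specify, beside the overall intention-to-treat result, a supportive Cox estimate split at visit 1, with hazard ratios before and after. Say in advance that the early one will be imprecise and that neither replaces the overall result.
3. State in Sample size whether 12% allows for the untreated month. If it does, give the ratio this implies once training starts. If it does not, give the power that remains under a stated early share.

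The cost is two short questionnaires at an existing visit, one extra analysis and a sentence of text. Moving randomisation to visit 1 remains an option for the sponsor to weigh against the change in population and outcome window.

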#### Data collection and management

We will collect information on outcome at each stage of recruitment, randomization, treatment allocation, follow-up, and analysis in order to report patient flow according to CONSORT guidelines [15]. We will record the number of patients who meet exclusion criteria, the number of patients who qualified for inclusion but who were not willing to participate, the number of patients assigned to the intervention arm, the number of patients assigned to the control arm, the number of intervention visits, the number of patients who provided follow-up data, the number of patients included in the analysis, and the number of withdrawals.

To ensure that clinical data collection forms are accurately entered into databases, we will periodically validate the information collected in the database (detection of missing and out-of-range values). To maintain the confidentiality of the information, all patients will be identified by study numbers.

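### The chi-square on the sized 12-month readmission percentage cannot use partial follow-up, so its result depends on how patients lost event-free are counted, which matters mainly if loss differs between arms

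*Protocol article*

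**What the plan says.** All references are to the protocol article.

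- **Sample size** names one test for the percentage of cardiac readmissions: "through a two-tailed chi-square test for two independent samples, with a level of significance of 0.05". Power is 80%, with 25% assumed in controls and 12% in the intervention arm. The result is given as "each group will require 139 patients. Assuming a 5% loss to follow-up", which brings the number to 146 per arm.
- **Statistical analysis** plans the same two-tailed chi-square for that percentage. Time to first cardiac readmission, also listed as primary, gets Kaplan-Meier, log-rank and Cox.
- Between the survival sentences of that section stands the only rule for incomplete follow-up. Information on the endpoints is collected to the last contact, "including patients lost to follow-up, at which point follow-up will be censored". Deaths without hospitalisation are censored in the survival analysis; their place in the chi-square is not given.
- The same section says "Outcomes will be analysed on an intention-to-treat basis".
- **Data collection and management** promises to report "the number of patients included in the analysis, and the number of withdrawals".

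**The concern.** A chi-square on a 12-month percentage needs a yes or no for every patient in the table. A patient who leaves at month 4 without a readmission has neither, and censoring is not a cell of the table. The analyst must choose:

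- **Score as not readmitted.** Readmissions after loss are missed, so the arm's risk is understated.
- **Drop.** If patients readmitted before loss stay in the table, as is natural because their status is known, only event-free patients leave the denominator and the arm's risk is overstated.

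The two errors have opposite signs. With equal loss they shift both arms alike. With unequal loss they push the treatment difference in opposite directions. The result of the one sized outcome could then turn on that choice, and could differ from the survival analysis of the same patients.

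**Working it through.** **1. The plan's own figure.** Inputs from Sample size: p1 = 0.25, p2 = 0.12, two-sided alpha 0.05, power 80%. For the uncorrected chi-square (pooled variance), with mean proportion 0.185:

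n = [1.960 × √(2 × 0.185 × 0.815) + 0.8416 × √(0.25 × 0.75 + 0.12 × 0.88)]² / 0.13²
= [1.960 × 0.5491 + 0.8416 × 0.5414]² / 0.0169 = (1.5319)² / 0.0169 = 138.9, so **139**.

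For loss, 139 × 1.05 = 145.95, so **146** (139 / 0.95 = 146.3 would round up to 147, a trivial difference). The sample size reproduces and is not at fault.

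**2. Expected percentages under the two handlings.** Assumptions, none of them in the documents: constant readmission hazard over the year, loss times uniform over the year, loss unrelated to readmission, no deaths. With 12-month risk p, hazard λ = −ln(1 − p) and loss fraction d, a patient who leaves has been readmitted beforehand with probability

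q = 1 − p/λ.

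- Control: λ = 0.2877, q = 1 − 0.25/0.2877 = 0.131.
- Intervention: λ = 0.1278, q = 1 − 0.12/0.1278 = 0.061.

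Scored as not readmitted: s = (1 − d)p + dq.
Event-free losses dropped: r = s / [1 − d(1 − q)].

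For 5% loss in both arms:

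- s = 0.95 × 0.25 + 0.05 × 0.131 = 24.4% and 0.95 × 0.12 + 0.05 × 0.061 = 11.7%, a difference of 12.7 points.
- r = 0.24405/0.95655 = 25.5% and 0.11706/0.95306 = 12.3%, a difference of 13.2 points.

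The other rows use the same formulas. Power and disagreement come from 40,000 simulated trials per row, 146 per arm, uncorrected chi-square. True difference 13.0 points.

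| Loss, control / intervention | Scored: rates, difference, power | Dropped: rates, difference, power | Opposite decisions |
|---|---|---|---|
| 5% / 5% | 24.4 v 11.7, 12.7, 82% | 25.5 v 12.3, 13.2, 82% | about 2% |
| 2% / 8% | 24.8 v 11.5, 13.2, 85% | 25.2 v 12.5, 12.7, 78% | about 6 to 7% |
| 0% / 10% | 25.0 v 11.4, 13.6, 86% | 25.0 v 12.6, 12.4, 76% | about 10% |
| 10% / 0% | 23.8 v 12.0, 11.8, 76% | 26.1 v 12.0, 14.1, 86% | about 10% |

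Simulated mean differences agree with the formulas to within 0.1 point; some runs gave 13.3 where the formula gives 13.2, and 12.8 where it gives 12.7.

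**3. A single table.** Suppose 14 of 292 patients (4.8%) are lost event-free, 3 in control and 11 in intervention, with 30 v 17 readmissions.

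- Scored: 30/146 v 17/146. Difference 0.0890, pooled standard error √(0.1610 × 0.8390 × 2/146) = 0.0430, z = 2.07, p = 0.038.
- Dropped: 30/143 v 17/135. Difference 0.0839, standard error √(0.1691 × 0.8309 × (1/143 + 1/135)) = 0.0450, z = 1.86, p = 0.062.

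With the losses split 7 and 7, none of the tables checked (25 to 39 control readmissions) changed side of 0.05.

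**4. No true effect (25% in both arms).** At 2% v 8% loss both handlings reject in about 5% of trials. Rejection reaches about 6.5% only at an assumed 20% v 5%, far above the planned loss.

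**5. An estimate that uses partial follow-up.** The 12-month cumulative incidence difference, tested by z from its own standard error, gives 13.0 points and about 82% power in all the effect rows above, and close to 5% rejection under no effect.

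**The case against.** The strongest reply is that this is an omission, not an error. The censoring sentence sits among survival sentences, where it can be carried out, and nothing tells the analyst to censor in the chi-square. Handling of missing binary outcomes is commonly left to a full protocol or analysis plan, neither of which is shown. That is right as far as it goes. What remains is that the article itself fixes a test that cannot use partial follow-up while expecting some loss, although the dates a better estimate needs are already to be collected.

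A reader might also infer that the document contradicts itself: intention-to-treat would require all 146 per arm, and the step from 139 to 146 would require lost patients to be dropped. The text does not support this. Intention-to-treat fixes the arm in which a patient is analysed, not how an unknown outcome is scored. The inflation is a routine allowance for lost information and defines no denominator.

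Nor do the documents show that loss will differ by arm. Only the intervention arm attends supervised sessions three times a week for 10 weeks, but missing sessions is not loss to follow-up, and both arms have the same nurse visits at 1, 3, 6 and 12 months. Limitations raises distance and transport for inclusion, not retention.

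Two further points stand. Dropping every lost patient, including those already readmitted, is unbiased under the assumptions above (13.0 points, about 5% rejection under no effect), so the overstatement belongs only to dropping event-free losses. And time to first readmission already handles censoring, so the problem is confined to the chi-square result.

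**Conclusion.** The point holds as a worthwhile, inexpensive improvement. At the planned 5% loss, if balanced, the choice is negligible: 12.7 v 13.2 points around a true 13.0, and equal power. If loss differs by arm, the choice can decide a borderline result: a power gap of about 7 percentage points at 2% v 8% loss and about 10 at 0% v 10%. These figures rest on assumed loss splits, constant hazard, uniform loss times and non-informative loss.

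The working does not support the stronger claims that the sample size is wrong or that the type I error is materially inflated at the planned loss. Priority lies between optional and recommended.

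**What to change.** In Statistical analysis, make the comparison of the 12-month percentage the between-arm difference in cumulative incidence of first cardiac readmission at 12 months:

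- Include all randomised patients in their assigned arm.
- Censor living patients with incomplete follow-up at last known status.
- Treat death without readmission as a competing event in this estimate, not as censored. With complete follow-up the estimate then equals the observed percentage; with deaths censored it would not.
- Report the 95% CI and a z-test from the standard error of the difference.

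Keep the chi-square among patients with known 12-month status as a sensitivity analysis, and say whether patients readmitted before loss are in it. If they are, it carries the overstatement shown above.

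The sample size stands approximately. The z-test with its own standard error corresponds to the unpooled formula, (1.960 + 0.8416)² × (0.1875 + 0.1056) / 0.0169 = 136.1 per arm, against 139 for the pooled chi-square.

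The cost is a change of wording and slightly more analysis work; the dates are already needed for Kaplan-Meier. The method still assumes that loss is non-informative. If the chi-square is kept as the main test, the minimum is one sentence fixing its denominator, the scoring of event-free losses and the place of deaths.
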